Below is the trial protocol approved by the Aurora IRB prior to the beginning of the trial. For primary and secondary outcomes, please refer to the trial registries:

<https://clinicaltrials.gov/ct2/show/NCT02996045>

<https://www.socialscienceregistry.org/trials/1846>

**SPONSOR**

MIT is the author of the protocol and the main grant awardee. Aurora Health Care is the potential sub-awardee of a grant from the Laura and John Arnold Foundation (LJAF).

**Version Date: July 13, 2016 (replaces** May 19, 2016)

**BACKGROUND AND SIGNIFICANCE**

In 2008, the Congressional Budget Office identified inappropriate use of health services as a major contributor to health care spending inefficiency [1]. In 2013, the Medicare Payment Advisory Commission (MedPAC) identified the inappropriate use of diagnostic imaging as a large part of the problem [2]. It is estimated that one third of imaging procedures are not warranted, costing between $3 billion to $10 billion annually while there is no clear guidance on clinical effectiveness (i.e., more tests do not result in better health outcomes; on the contrary they might even lead to unnecessary exposure to radiation and subsequent testing) [3]. The issue holds for both the inpatient and ambulatory setting. In a study conducted in the ambulatory setting rates of as high as 62% (for CT of the head) of inappropriate use of imaging were found. Moreover, the study also demonstrated higher rates of negative results when tests were deemed inappropriate (47%) versus those that were deemed appropriate (20%) [4].

**Clinical Decision Support (CDS)**

Health information technology has the potential to remind providers about appropriate health utilization [1]. Many health insurers are now using 'radiology benefit management' programs to reimburse imaging use by evaluating them against pre-specified appropriateness criteria [3]. Another option that is being utilized is Clinical Decision Support (CDS) software. CDS generally refers to the use of software systems to improve clinical decision-making, and involves matching patient characteristics to evidence-based guidelines to provide clinicians with clinically relevant information at the time of order entry.

In particular, we intend to study the use of a tool called ACR Select[7]. ACR Select is the electronic version of the American College of Radiology's Appropriateness Criteria at point of order and is considered the industry standard. When ordering a scan through Epic’s order entry system, providers choose a clinical indication and a particular scan (e.g. the indication is a headache and the scan is a CT Scan of the Head). The patient’s age and gender, along with the indication and scan are then evaluated against the ACR guidelines. A best-practice alert (BPA) can then be generated—a pop-up screen that describes the results. Scores range from 1-9, with 1 being the least appropriate and 9 the most. In accordance with the Appropriateness Criteria, the numeric scores are grouped into three categories for the purpose of providing recommendations to decision-makers: 1-3 is deemed “usually not appropriate”, 4-6 “may be appropriate”, and 7-9 “usually appropriate.” The Appropriateness Criteria represent a national standard and were developed by an interdisciplinary panel of experts in the field of radiology and medicine to determine appropriate/inappropriate use of diagnostic imaging.

A typical BPA screen looks like this (We are in the process of editing this to include a note on the top that says “Unless further action is taken in the checkboxes below, CT HEAD W CONTRAST will be removed from orders":

[figure not shown]

Results from observational pre-post studies suggest that the introduction of such clinical decision support systems in outpatient radiology may reduce high-cost scanning by about 20% overall, and reduce the rate of “inappropriate” scanning by 20-70%. [5, 6]. However, there has never been a randomized trial of the impact of CDS for radiology orders, which leaves considerable uncertainty about the impact of CDS for radiology. For example, it is possible that the estimated impact of CDS in pre-post studies is contaminated by other initiatives or changes going on in the healthcare system at the same time that CDS was introduced. The researchers involved in this study are currently implementing a randomized trial in another setting, and hope to combine evidence from multiple settings to generate a body of evidence around CDS.

**CDS at Aurora**

Aurora Health Care implemented ACR select in October 2015. It is currently running “in the background” with no best-practice alerts being shown to providers. Best practice alerts will begin to be shown to providers in the near future in part because of new federal regulations. It is important to note that providers maintain their authority over imaging and treatment plans. The CDS intervention (Best Practice Alert) is non-obtrusive and can be easily overridden by the provider.

The Protecting Access to Medicare Act (PAMA) of 2014 [9] stipulates that provider-led entity developed CDS (such as ACR Select) must be consulted at the time of order entry for advanced diagnostic imaging performed on ambulatory Medicare patients. (Originally, the law specified January 1, 2017. The most recent regulatory commentary states that it will not be mandated by January 1, 2017 but does not specify when it will be mandated.) The law defines the ambulatory setting as inclusive of the provider office building or clinic, outpatient imaging performed in a hospital, the Emergency department, and the ambulatory surgery center. If proof of CDS consultation at order entry and a measure of how well the choice of imaging aligns with the appropriateness criteria are not attached to each Medicare claim, both the technical and professional reimbursement for the exam will be forfeit. Nearly all of Aurora Health Care's AboutHealth partners have implemented or are in the process of implementing CDS for advanced imaging across their systems, both inpatient and outpatient. To comply with the law and to stand with our partners in providing the most appropriate imaging care, Aurora Health Care has also done this.

While all providers are now entering a clinical indication for exam, the appropriateness is being scored in the background and stored without being shown to providers. This step, which is commonly taken by systems implementing CDS, allows measurement of baseline imaging utilization and appropriateness. We anticipate that when the mandate takes effect, the appropriateness scores and associated clinical decision support will be shown to all ordering providers at the point of order entry.

Our study will allow Aurora to understand the value of the CDS tool for providers and patients and also helps roll out the system in a systematic way to anticipate effects of complying with the law. As CMS has expressed informal interest in the results of this study, it may impact healthcare delivery nationally. This proposal has been outlined to and received support from Aurora Health Care's senior leadership.

**OBJECTIVE**

The overall goal of this research is to evaluate the impact of a CDS system on the appropriateness of advanced imaging ordering.

We aim to determine whether decision support will:

1. Lower the rate of low utility scans (ACR scored 1-3).

2. Lower the rate of high-costs scans.

3. Affect downstream utilization. Decision support could, in theory, increase, decrease, or leave these costs unchanged.

**ENDOINTS**

Primary endpoints are:

- Ordering rate of scans of low utility (ACR score 1-3). This will be recorded as the number of inappropriate scans and the number of inappropriate scans per visit to the provider

- Provider diagnostic imaging rates: # of CT, # of MRI and # of total CT and MRI scans, as well as these measures per visit to the provider

Secondary endpoints are:

- Indication of change or cancellation of a scan

- Indicators of subsequent healthcare utilization/costs, such as:

• Subsequent scans

• ED visits

• Clinic visits

• Inpatient admission rate

• Number of inpatient admissions

• Procedures

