**EXPERIMENTAL DESIGN AND METHODS**

We propose a prospective, randomized controlled trial to measure the impact of CDS. Providers will be randomized into two arms: a treatment group that will receive feedback from the CDS system and a control group that does not.

- Aurora will send MIT a list of providers (encrypted IDs).  This will be for all providers who ordered an exam over the past 2 years who did not opt out of the study.
- MIT will randomize and create an indicator for treatment/control

(=0 or 1)

- MIT will send the encrypted IDs and their treatment indicator to Aurora
- Aurora will attach the treatment indicator to actual provider IDs
- The actual provider IDs and treatment indicator will then be sent by Aurora to NDSC*
- The order-entry system sends the order details, including the provider ID, to NDSC.  NDSC will write a script to display the best practice alerts only to those provider IDs in the treatment group.

Aurora will create and maintain the actual ID - encrypted ID crosswalk.

This will not be provided to MIT or NDSC.

*NDSC is the national decision support company. They provide the ACR Select

software. The provider ID will be sent to NDSC as part of the implementation

of ACR Select – and is not a research piece.

The CDS consists of several (bundled) components:

1. **Require selection of indication.** In order to properly score as many scans as possible, the order-entry software has been configured to require ordering providers to select a discrete indication from an existing list. This has been and will continue to be required of all providers: both treatment and control.
2. **Optional textbox to clarify indication selection**. There is an *optional* free-text box below the indication that allows providers to provide relevant additional clinical information for radiologists. This is available to all providers: both treatment and control.

The remaining features will be turned on only for providers in the treatment group and for providers who have opted out of the study. The below specifics are a business decision and a starting point for this project, independent of the research, and as such, are subject to modification.

1. **Display CDS at provider sign-off .** The CDS displays as a pop-up screen which appears when providers attempt to sign off on a scan. [name] will work with informatics physician leaders to determine a firing logic which minimizes provider alert fatigue.

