2. **Only show appropriateness score.** The decision support tool will only show the appropriateness score, not costs or radiation exposure levels – though costs and radiation exposure levels are options on the CDS software.
3. **Only display alternative scans with a score of 7-9.** Only alternative scans with scores greater than 6 will be displayed in the CDS window. Only the highest rated scan alternative(s) will appear as “suggested” alternatives, while other alternative scans rated 7-9 will appear in the CDS window in order of appropriateness (*i.e.* first is the highest rated scan, etc.). This is an attempt to make it easiest to order the “most appropriate” alternative scan.
4. **Default to cancel scans.** Any time the CDS pop-up appears, a checkbox to remove the selected scan will be checked by default. This default can be over-ridden by the ordering provider by de-selecting the checkbox.^[[1]](#footnote-1)^
5. **Provide relevant ACR documentation.** A link to ACR documentation relevant to the indication category will be provided in the pop-up window.

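### The low-utility endpoint rests on an indication the ordering provider picks, and only the treated arm sees the resulting score, so a fall in 1-3 orders needs supporting counts before it is read as less low-value imaging

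*Protocol*

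**What the plan says.** All references are to the Protocol.

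- **Endpoint (ENDOINTS, as the heading is printed).** The first primary endpoint is "Ordering rate of scans of low utility (ACR score 1-3"), as a count and per visit. The second is the number of CT, MRI and total scans, which does not use the score. A secondary endpoint records a change or cancellation of a scan; a change of indication is not named.
- **How the score arises (Clinical Decision Support).** At order entry "providers choose a clinical indication and a particular scan". The patient's age and gender, "along with the indication and scan are then evaluated against the ACR guidelines".
- **Who supplies the indication (EXPERIMENTAL DESIGN AND METHODS).** In both arms the software is set to "require ordering providers to select a discrete indication from an existing list". The reason given is "In order to properly score as many scans as possible", which implies that some scans stay unscored. The section gives no unscored share.
- **Who sees the score (same section).** "NDSC will write a script to display the best practice alerts only to those provider IDs in the treatment group". "The CDS displays as a pop-up screen which appears when providers attempt to sign off on a scan", so it follows the choice of indication. "The decision support tool will only show the appropriateness score", not cost or radiation, and removal of the scan is ticked by default. Control providers get no feedback.
- **Analysis (STATISTICAL PLAN).** Provider-level regression on assignment, with the quiet-period value of the outcome as the only covariate in the main specification.

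**The concern.** One input to the outcome measure is set by the person being randomised, and only one arm is told how that input scores. If treated providers come to choose other indications for the same patient and scan, or if more of their orders go unscored, orders leave the 1-3 count while the same scans are still done. This would be a difference in measurement between arms that arises after randomisation and because of it. Balanced arms do not prevent it, and a covariate measured before launch cannot adjust for it.

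The Protocol itself expects treated providers to learn from the alerts (its argument for waiving patient consent says so). Feedback that teaches which scans suit which indications could also teach which indications score well.

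At stake is the meaning of a positive result. The objective concerns the appropriateness of ordering, and the background section says the findings may influence care nationally. A fall in 1-3 orders alone would not tell fewer low-value scans from differently labelled ones.

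**Working it through.** **Inputs from Statistical Power:** N = 3506 providers; detectable reduction 20% for high-cost scans and 15% for inappropriate scans; inappropriate rate about 10%.

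**Assumptions (not in the Protocol):** 1:1 allocation (1753 per arm), two-sided 5% level, 80% power, the 10% read as a share of scans, and high-cost scans taken to mean the total CT and MRI count.

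**1. The plan's own figures.** They come from simulation, and the level, power and SD are not given, so they cannot be reproduced independently. Solving backwards instead:

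SD/mean = effect / [(1.96 + 0.84) × √(2/1753)] = effect / 0.0946

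This gives 0.20/0.0946 = 2.11 for high-cost scans and 0.15/0.0946 = 1.59 for inappropriate scans. With one- or two-sided 5% and 80-90% power, the ranges are 1.83-2.38 and 1.37-1.79. These values are calibrated to the plan and do not check it.

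**2. Relabelling with no scan avoided.** Let g be the share of treated-arm 1-3 orders that move to a score of 4 or more, or to unscored. The treated rate is 10 × (1 − g) per 100 scans, so the relative fall is g. The chance of a significant result is Φ(g / [1.59 × √(2/1753)] − 1.96).

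| g (illustrative) | 1-3 orders per 100 scans | Relabelled, % of all scans | Chance of significance |
|---|---|---|---|
| 5% | 9.5 | 0.5 | 15% |
| 10% | 9.0 | 1.0 | 46% |
| 15% | 8.5 | 1.5 | 80% |
| 20% | 8.0 | 2.0 | 96% |

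The 80% at g = 15% follows from the calibration. It restates the plan's detectable effect and is not a separate finding.

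**3. Differential non-scoring.** If shares u0 (control) and u1 (treated) of orders that would score 1-3 go unscored, the apparent fall is 1 − (1 − u1)/(1 − u0).

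- 10% against 15%: 1 − 0.85/0.90 = 5.6%.
- 10% against 20%: 1 − 0.80/0.90 = 11.1%.
- 10% against 23.5%: 1 − 0.765/0.90 = 15%.
- 20% against 32%: 1 − 0.68/0.80 = 15%.

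**4. Can the total-scan endpoint tell the two apart?** A wholly real 15% fall, all through cancellation, lowers total scans by 0.10 × 15% = 1.5% (0.75-2.25% for a base rate of 5-15%). A wholly relabelled fall lowers them by 0%. Power to see 1.5% with SD/mean 2.11 is about 5.5%. Cancelling every 1-3 scan would lower the total by 10%, with power of about 29%. On total scans the two cases look alike.

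**5. What a combined count of 1-3 and unscored orders can show.** Let U be unscored orders per 100 scans in control, so the control value is 10 + U. Take g = 15%.

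- All moved to unscored: 8.5 + U + 1.5 = 10 + U, no change.
- All moved to a score of 4 or more: 8.5 + U, a fall of 1.5.
- All cancelled: 8.5 + U, a fall of 1.5.

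The combined count exposes the unscored route but not a shift to better-scoring indications. That needs the indication mix.

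**The case against.** The strongest reply is that the behaviour is nowhere described. The actions set out for the pop-up are removing the scan, unticking that default, taking a higher-scored alternative and opening the guideline link. Editing the indication is not among them, and no unscorable list entry is mentioned. CDS at Aurora calls the alert easy to override, and the risk section puts ordering after an alert at two clicks whichever scan is kept. A provider who wants the scan has little need to relabel it. This stands. A reader might infer that treated providers can and will re-enter orders under a better-scoring or unscorable indication, so that the endpoint is biased towards the intervention. The Protocol does not support that as fact.

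It is also fair to say that g is chosen rather than estimated, that a fall with no scan avoided can be a success (switching to a better-scored scan is intended), and that some changes of indication are honest corrections. All of this stands.

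The remaining replies carry less weight. The score-free CT and MRI endpoint is a sensible safeguard in design, but step 4 shows that it is too coarse for this purpose. An SAP may add sensitivity analyses, and the attached variable list, which is not shown, may already hold the needed fields. That affects how much must be added. It does not change how this primary endpoint is measured.

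**Conclusion.** The concern holds as a limit on interpretation. Measurement of the first primary endpoint can differ by arm, and neither randomisation nor the lagged outcome would correct that. Whether it will differ, and by how much, is unknown. Relabelling 5-20% of treated-arm 1-3 orders would lower the endpoint by 5-20%, on the scale of the stated detectable 15%. It would touch only 0.5-2% of scans if the 10% rate is a share of scans, far below the 20% stated as detectable for high-cost scans. The relabelled shares are illustrations. The probabilities also rest on the assumed allocation, level and power.

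It would go too far to say that a fall in 1-3 orders will be an artefact, or that the endpoint is unfit to be primary. It is a reasonable primary endpoint that needs supporting evidence, and adding that evidence is advisable.

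**What to change.** Keep the 1-3 count, and the count per visit, as the primary endpoint, and prespecify the following:

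1. A supporting regression in the same model on 1-3 plus unscored orders, with its own quiet-period lag.
2. By-arm comparisons of the unscored share and of the mix of selected indications within scan type.
3. A by-arm comparison of first-to-final indication changes, where the decision-support vendor's data hold them. That vendor is already a data source under DATA COLLECTION.
4. A reporting rule: a fall in 1-3 orders is described as less low-value imaging only with items 1 to 3 shown alongside.

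Two tempting alternatives are not advised. Classifying every order by the first indication entered would count honest corrections as low-value scans, and it would miss providers who learn to enter a better-scoring indication first. Making a fall in the combined count a sufficient condition for the claim would also fail, because that count falls in the same way when orders move to indications scoring 4 or more (step 5).

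The cost is a few extra regressions and data fields. One weakness remains: a difference in indication mix may partly reflect honest correction, so it informs the reading of the result without settling it.

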**STATISTICAL PLAN**

The main analysis will compare outcomes for providers who were randomized to receive CDS compared to those who were randomized to the control group using regression analysis. MIT will perform the data analysis. They will compute Intent-to-Treat estimates as our primary method.

Consider an outcome, Y , such as the number of non-advised scans ordered by each provider provider. For provider i, the estimating equation is:

$$Y_{i}=\beta_{0}+\beta_{1}{1(\text{Treatment})}_{i}+\beta_{2}X_{i}+\varepsilon_{i}$$

where Treatment_i is an indicator variable equal to one if the visiting provider was randomized to the treatment group and zero if the provider was randomized to the control group; X_i is a vector of control variables. These control variables should be uncorrelated with the treatment indicator, but they can aid in the precision of the estimate. For our main specification, we will include only the lagged dependent variable (defined during the quiet period prior to study launch) since this generates a first order improvement in power to estimate an effect of the CDS. As robustness checks, we will examine these regressions without any controls as well as controlling for the full set of observable provider characteristics.

$\beta_{1}$ is the parameter of interest and measures the Intent to Treat (ITT): the causal effect of a provider being randomized into the treatment group.

Sometimes the provider who orders the scan is not the same as the provider the patient initially visits. One robustness check will use the treatment status of the visiting provider as an instrument for the treatment status of the provider who orders the scan in order to compute Local Average Treatment Effect (LATE) estimates.

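### The provider-level ordering counts cannot by themselves tell a scan avoided from one later ordered by an alert-free control colleague, so they may overstate scans avoided

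*Protocol*

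**What the plan says.** The second aim in the Protocol, section OBJECTIVE, is to find out whether decision support will "Lower the rate of high-costs scans"; the first aim is the same for scans scored 1 to 3. Section ENDOINTS (so spelled) makes two families of measures primary: for low-utility scans, "the number of inappropriate scans and the number of inappropriate scans per visit to the provider"; for volume, "Provider diagnostic imaging rates: # of CT, # of MRI and # of total CT and MRI scans", each also taken per visit. Subsequent scans are listed separately, as a secondary endpoint.

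Allocation is by individual provider within one health system. Section EXPERIMENTAL DESIGN AND METHODS states that "NDSC will write a script to display the best practice alerts only to those provider IDs in the treatment group". When the alert appears, removal of the scan is pre-ticked. Providers who opt out also see the alert, are not randomised, and the orders they place are not analysed.

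Section STATISTICAL PLAN gives as its example outcome "the number of non-advised scans ordered by each provider", but defines the treatment indicator by the arm of the visiting provider. It notes that the visited and ordering providers sometimes differ, and answers this with one robustness check that uses the visited provider's arm as an instrument for the ordering provider's arm.

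**The concern.** The alert belongs to the person who signs the order, while the patient can move between people who do and do not see it. If a treated provider drops a scan and a control colleague later orders it, the treated count falls by one and the control count rises by one, yet the patient has still been scanned. The contrast then records a difference where nothing was avoided.

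This matters for how the result is read. The first two aims ask whether scan rates fall, and section CDS at Aurora expects that all ordering providers will eventually see the alert. At that point no alert-free colleague remains, so a difference that came partly from moved orders would not carry over to full roll-out.

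Neither existing safeguard closes the gap. The instrumental-variable check addresses a mismatch between visited and ordering provider; it does not net moved orders out of the primary contrast. Subsequent scans could reveal some re-ordering, but they are reported as a separate endpoint.

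**Working it through.** **The plan's own figures.** The protocol gives no figure for re-ordering or for spillover between arms. The nearest figures, in section Statistical Power, are detectable reductions of 20% in high-cost scans and 15% in inappropriate scans, from simulations on 3506 providers and a 12-month study. No significance level, power, allocation ratio or variance is stated, so they cannot be reproduced. Nothing below depends on them, except that 20% is borrowed as an illustrative size.

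**Inputs**
- From the protocol: individual randomisation, an alert keyed to the ordering ID, and an outcome counted by ordering provider.
- Assumed: equal arms; a mean of 1 scan per provider without alerts; treated providers drop a share e of their scans; a share d of the dropped scans is then ordered by colleagues.

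**Net scans avoided** among treated providers' patients: e − de = e(1−d).

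**Measured contrast when all re-orders go to controls.** Treated mean 1−e, control mean 1+de, difference e(1+d). Ratio to scans avoided: (1+d)/(1−d).

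**Measured contrast when re-orders spread evenly over both arms.** Treated mean 1−e+de/2, control mean 1+de/2, difference e. Ratio: 1/(1−d). The ratio is the same if re-orders fall outside both counts, for example to providers who opted out (treated 1−e, control 1).

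| d | Ratio, even spread | Ratio, all to controls | Net avoided, e = 0.20 | Measured, e = 0.20 |
|---|---|---|---|---|
| 0% | 1.00 | 1.00 | 0.20 | 0.20 |
| 5% | 1/0.95 = 1.05 | 1.05/0.95 = 1.11 | 0.19 | 0.20 to 0.21 |
| 10% | 1/0.90 = 1.11 | 1.10/0.90 = 1.22 | 0.18 | 0.20 to 0.22 |
| 25% | 1/0.75 = 1.33 | 1.25/0.75 = 1.67 | 0.15 | 0.20 to 0.25 |

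The ratios do not depend on e. Differences are in units of the baseline mean. As a share of the raised control mean, the 0.25 in the last row is 0.25/1.05 = 0.238.

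**Attribution.** If scans are credited to the visited provider, a re-order within the same encounter stays with the treated visit and causes no bias. A re-order at a new visit to a control colleague still moves between arms. The protocol mixes the two rules, so which case applies is not settled.

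**ACR 1 to 3 scans.** The control count of low-utility scans rises only if the colleague's order also scores 1 to 3. For this endpoint d is therefore the share of dropped low-score scans re-ordered as scans that again score 1 to 3. If the colleague orders a higher-scoring alternative, the fall in low-utility scans is real.

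**Spillover in the other direction.** Suppose controls also cut their ordering by se because knowledge of the criteria spreads. With all re-orders going to controls, the contrast is e(1+d−s), which equals e(1−d) when s = 2d. With even spread it is e(1−s), which equals e(1−d) when s = d. At d = 10% these points are s = 20% and s = 10%. Beyond them the contrast understates avoidance: with d = 10%, s = 30% and all re-orders to controls, the ratio is (1.10−0.30)/0.90 = 0.89.

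**The case against.** The strongest reply is that the protocol shows a route for moved orders but no traffic on it. It says that visited and ordering providers sometimes differ, not that dropped orders pass to colleagues. By section POTENTIAL RISKS AND BENEFITS (Providers), completing an order after an alert takes two clicks, so a treated provider who still wants the scan has an easier route than a colleague. That stands, and makes large values of d less likely. It does not exclude a second provider who later sees the patient and orders independently.

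A second reply is that the provider-level intention-to-treat contrast answers a legitimate question, how alerts change a provider's own ordering, and that the endpoints are worded as ordering and provider rates. This also stands. It is why the ordering counts should remain primary, and why a patient-level count, whose power has not been assessed, should not replace them.

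A reader might infer that the primary counts do overstate avoidance, or that the bias must favour the tool. The document supports neither. It gives no frequency of re-ordering, the bias is zero at d = 0, and section Informed Consent (the case for waiving patient consent) expects providers to learn from the alerts. If that learning reaches controls, it pulls the contrast the other way.

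**Conclusion.** The concern holds as a limit on interpretation. The provider-level ordering counts cannot by themselves separate a scan avoided from one moved to an alert-free colleague, and nothing in the protocol nets moved orders out of the primary contrast. The possible overstatement runs from none at d = 0, through 1.05 to 1.11 at 5% and 1.11 to 1.22 at 10%, to 1.33 to 1.67 at 25%. These factors assume equal arms, no spread of learning to controls and, for low-utility scans, that the re-order also scores 1 to 3. The value of d is an assumption throughout, and the net direction is unknown once learning is allowed for. The contrast remains valid as a description of providers' own ordering under partial roll-out. The protocol sends readers to the registries for outcomes, and neither those nor a SAP was seen; this judgement rests on the protocol text alone.

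**What to change.** 1. Keep the provider-level ordering counts as primary and label them the effect on providers' own ordering. Use one attribution rule in ENDOINTS and STATISTICAL PLAN: the treatment indicator should be the arm of the same provider whose orders are counted.
2. Pre-specify a key supportive analysis. For each visit to a randomised provider, count CT and MRI scans, and separately ACR 1 to 3 scans, ordered for that patient by any provider within a fixed window. Assign the count to the arm of the first-visited provider, and count each scan once. Choose the window before outcomes are seen by arm.
3. Report this net count beside the primary result. Word the conclusion as scans avoided only if the net count also falls, with the criterion for a fall set in advance; otherwise describe a change in provider ordering.

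**Cost.** This is mainly analysis work. By section DATA COLLECTION, the extract is already at encounter-scan level with proxy identifiers for patients and ordering providers. The team should confirm that the variable list also carries the visited provider, which the instrumental-variable check needs anyway. The net count is diluted by unrelated scans in the window and by patients who see both arms, and will be less precise; the protocol's power simulation does not cover it. Orders by providers who opted out stay invisible, because the protocol bars their analysis, so the count means any provider whose orders may be analysed.
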